## Autonomy

Modified Barthel Index; location of eating, eliminating urine or stool, and washing

Comorbidities will be collected according to the Charlson Comorbidity Index.

Autonomy in the activities of daily living prior to hospitalization will be assessed at admission using the modified Barthel Index in a face-to-face interview (for description of the modified Barthel Index, see section 2.2.3). For patients with cognitive impairment or confusion, the level of autonomy before hospitalization will be assessed by interviewing their relatives or caregivers, in face-to-face interviews or by phone call.

Data will be collected from electronic health records, except for information such as data on contact details, mobility, paresis/paralysis, recent travel, dehydration, leg, edema, and patient autonomy, which will be collected at the patient bedside (from the patient and/or nurse in charge) by trained study nurses.

At baseline, the simplified and original Geneva score, the IMPROVE score, and the Padua score will be calculated and patients will be categorized as high or low VTE risk according to each RAM (**Table 1**). Treating physicians will not be informed of the patients' scores, and no specific recommendations concerning the use of a RAM or TPX will be made. Thus, the use of TPX will not be influenced by the study.

### 3.3.3.2 Mobility measurements

Because immobilization criteria defined in each RAM consider the patient's ability or inability to move and its duration (**Table 1**), we will objectively assess periods of mobility in all eligible and consenting patients using a wrist-worn tri-axis accelerometer (GENEActiv Original, ActivInsights Ltd, UK, <https://www.activinsights.com/actigraphy/geneactiv-original/>), parametrized at 50 Hz. These accelerometers have been shown to provide a reliable and valid measurement of physical activity in adults and hospitalized patients. The devices will be provided to the patients immediately after inclusion and patients will choose on which wrist they prefer to wear the device. Previous studies have shown that measuring site does not influence measurement. Patients will be asked to wear the device continuously (day and night, including showering) until hospital discharge or transfer to another department (e.g. intensive care, surgery unit). Accelerometry data will be extracted and analyzed using the GGIR package for R (version 1.11 or later). A valid day will be defined as at least 10 hours of daytime wear, and at least 24 hours of valid data will be required for analysis. In the analysis, we will consider the following measurements: minutes/day in different type of activities, no activity or sleep; total minutes during day spent active/inactive; mean acceleration in miliG/vector.

Physical activity raw data will be further processed using the open source GENEAcclassify R-package (<https://cran.r-project.org/web/packages/GENEAcclassify/GENEAcclassify.pdf>) in order to obtain the number of steps taken per day, the mean cadence, and the maximum gait speed (m/s). We will estimate the percentage of time of patient's mobility, using a cut-off of <4 steps and ≥4 steps taken per minute to define periods of immobilization and mobilization respectively, as previously reported in a study of medical inpatients.

At baseline, patients will be asked about their ability to walk, i.e. whether they are able to walk independently, with assistance from one or two persons, with or without mobility aids, or if they are not able to walk. In addition, we will assess from medical records whether physical therapy has been prescribed for mobilization.

On the second day of admission, study nurses will ask the treating physicians to judge whether their patients fulfill the different immobilization criteria as defined in each RAM (**Table 1**):

- for the simplified and original Geneva score: complete bedrest or inability to walk for >30min per day for ≥3 days
- for the Padua score: anticipated bed rest with bathroom privileges for ≥3 days
- for the IMPROVE score: patient is confined to bed or chair with or without bathroom privileges for ≥7 days immediately prior to and during hospital admission.

The treating physicians will also be asked to subjectively estimate the patient's mobility level in standardized terms (i.e., no ambulation, out of bed to chair, out of bed to ambulate once daily, twice or 3 times daily, or ambulate ad libitum). Physicians will be contacted on the second day of hospitalization rather than on admission because the decision to prescribe TPX is most likely already made on the second hospital day and thus less likely to be influenced by questions on the patient's mobility status. Prescriptions of specific ambulation regimens or physical therapy will be left at the discretion of the treating physician.

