## 2.2 Primary and secondary endpoints

### 2.2.1 Primary endpoint

The primary outcome will be symptomatic, objectively confirmed fatal and non-fatal HA-VTE, including symptomatic distal and proximal DVT and PE up to 90 days after hospital admission.

The objective diagnostic criteria for a PE diagnosis will be based on available radiographic or autopsy reports, and will include a new intraluminal filling defect on computed tomography pulmonary angiography (CTPA) or pulmonary angiography; a perfusion defect involving at least 75% of a segment, with corresponding normal ventilation (i.e., high probability lung scan); the confirmation of a new PE on autopsy, or an objectively confirmed proximal DVT with clinical signs and symptoms of PE. The objective diagnosis of DVT will be the non-compressibility of a venous segment on compression ultrasonography or an intraluminal filling defect on contrast venography. Because iliac veins and the inferior vena cava may be technically difficult to compress, additional diagnostic criteria for iliac and caval DVT will also include abnormal duplex flow patterns compatible with thrombosis or an intraluminal filling defect on spiral computed tomography or magnetic resonance imaging venography. We will consider both proximal and distal symptomatic DVTs. In line with previous studies on VTE prophylaxis and given similarities in some risk factors and outcomes, symptomatic upper extremity DVT will also be considered as a study outcome, although its incidence is expected to be low. VTE events diagnosed during the first 48 hours of hospitalization will not be considered as a primary outcome for this study in order to rule out pre-existing VTE that occurred prior to hospital admission.

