| Feasibility Substudy              |                                 |                      |                     |                                     |                  |
| Consent for hypothetical RCT                         |                                 |                      |                     | x                                   |                  |
| Medical Outcomes                              |                                 |                      |                     |                                     |                  |
| Symptomatic HA-VTE                                   |                                 |                      |                     | x                                   | x                |
| All-cause mortality                                  |                                 |                      |                     | x                                   | x                |
| Major bleeding                                       |                                 |                      |                     | x                                   | x                |
| Clinically relevant non-major bleeding               |                                 |                      |                     | x                                   | x                |
| Other study data                              |                                 |                      |                     |                                     |                  |
| Length of hospital stay                              |                                 |                      |                     | x                                   |                  |
| Discharge location                                   |                                 |                      |                     | x                                   |                  |
| Duration of VTE prophylaxis                          |                                 |                      |                     | x                                   |                  |
| Subsequent hospitalizations                          |                                 |                      |                     |                                     | x                |

 Enrolment and baseline visit may take place within 72 hours of admission

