### 3.3.3 Enrolment and Baseline

#### 3.3.3.1 Baseline data collection

After study inclusion, study personnel will collect the participants' contact details (name, date of birth, address, phone number, e-mail, contact details of the primary care physician and of a surrogate). This is necessary in order to contact the patients for the follow-up phone calls (or a surrogate in case the patient cannot be reached or has cognitive impairment) and to collect outcome data. These identifying data will be securely stored at the local study site and not be entered in the research database. For all eligible and consenting participants, study personnel will prospectively collect baseline data to describe the study population and for use as adjustment variables in statistical analyses. Following baseline data will be collected (**Table 4**): a) demographic data; b) all items of the simplified and original Geneva score, IMPROVE score, and Padua score (**Table 1**); c) comorbidities d) potential contraindications for pharmacological TPX; e) laboratory findings that are relevant concerning VTE or bleeding risk; f) medications at admission with a potential antithrombotic effect; g) treatments during the current hospital stay, including start date and type of TPX, defined as any use of pharmacological (unfractionated or low-molecular-weight heparin, fondaparinux, or direct oral anticoagulants) or mechanical (intermittent pneumatic compression devices or compression stockings) TPX, as well as other treatments potentially affecting risk of HA-VTE or bleeding; h) information on patient's autonomy.

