Work package 2) We will examine the association between subjective (physician's perception) and objective (accelerometry-measured) mobility levels, as a continuous measure as well as divided into quartiles, and 90-day cumulative incidences of HA-VTE using competing risk regression (accounting for non-VTE related death as a competing event), unadjusted as well as adjusted for TPX and study site. To define an optimal cutoff for objective immobility, we will assess sensitivity and specificity at different mobility levels using time-dependent ROC-curve analysis accounting for censored data and competing events. To compare the predictive performance of the simplified Geneva score using the standard subjectively-assessed definition of immobilization (i.e. physician perception) versus using objective accelerometry-assessed mobility measures, we will use likelihood ratio tests and/or the Akaike information criterion (AIC) as well as the c-statistics in competing risk models; immobility measures will be used as single covariates, as well as incorporated in the simplified Geneva score. We will assess the net reclassification index to assess improvement in risk prediction if using the accelerometry-based instead of the subjective immobility measure for the simplified Geneva score.

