## **6 FURTHER ASPECTS**

### **6.1 Overall ethical considerations**

We will conduct this study in accordance with the Declaration of Helsinki, the ICH-GCP guidelines, and all applicable legal/regulatory requirements. Prior to initiation of the study, authorization by the local Ethics Committees shall be obtained.

Given the broad eligibility criteria, the results of this study will be generalizable to the population of hospitalized medical patients at risk of HA-VTE, i.e. those without intake of therapeutic anticoagulation.

Informed consent will be obtained from each participant prior to the conduct of any study related procedures. For participants who are unable to give informed consent due to mental illness or cognitive impairment, permission to participate in the study will be obtained from a legally authorized representative, as outlined in section 3.2. We will include patients with cognitive impairment/confusion as they are at increased risk of immobilization during hospital stay, with a consecutive increase in the risk of hospitalization-related adverse outcomes such as HA-VTE. Excluding these patients would limit the generalizability of the results and question their applicability to this population, for whom the study findings might have the greatest relevance (see section 6.3).

A prospective cohort design is the optimal study design and provides the highest quality data to meet the aim of this study, i.e. to validate the simplified Geneva score, to compare

existing VTE risk assessment models, and to assess the prognostic value of objectively measured mobility concerning the risk of HA-VTE. A longitudinal study design is necessary to investigate prognostic measures, and prospective data collection allows to have complete and standardized measurements of exposures prior to the occurrence of any outcomes; also, objective mobility measurement is only possible in a prospective manner.

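### Work package 2 does not limit accelerometry to time before the event, so objective immobility can look predictive of HA-VTE when it is not

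*Protocol*

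**What the plan says.** Recording. Section 3.3.3.2 states "The devices will be provided to the patients immediately after inclusion", and the wear rule is "Patients will be asked to wear the device continuously (day and night, including showering) until hospital discharge or transfer to another department". Table 3 adds "Enrolment and baseline visit may take place within 72 hours of admission", so wear can begin on day 3. The measures are daily summaries such as minutes active and steps. The validity rules are 10 hours of daytime wear for a valid day and "at least 24 hours of valid data will be required for analysis". The synopsis describes continuous measurement throughout the stay.

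Outcome. Section 2.2.1 defines HA-VTE "including symptomatic distal and proximal DVT and PE up to 90 days after hospital admission" and leaves out only events diagnosed in the first 48 hours. In-hospital events therefore count.

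Analysis. Section 4.1.2, work package 2, says "We will examine the association between subjective (physician's perception) and objective (accelerometry-measured) mobility levels", continuous and in quartiles, against 90-day HA-VTE in competing risk regression. The same measure feeds the ROC cutoff search, the c-statistics and the net reclassification index.

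Comparator. Section 3.3.3.2 has the treating physician judge immobility once, on the second day of admission. Table 3 places this on the day after inclusion, with a window of days 1 to 3.

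Timing claim. Section 6.1 justifies the design because "prospective data collection allows to have complete and standardized measurements of exposures prior to the occurrence of any outcomes".

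**The concern.** A predictor must be measured before the event it predicts. A patient who has a VTE on the ward may move less afterwards because of the VTE. If those days enter that patient's mobility level, low mobility is partly a consequence of the outcome, and the association, cutoff and reclassification gain all absorb it. Only accelerometry is exposed to this over the whole stay; the physician's rating is a single early reading. The contrast at the centre of work package 2, objective against subjective immobility, is therefore unequal in timing as well as in method. Sections 1.2 and 2.1 want a threshold to inform prophylaxis decisions and a later mobility intervention, and reverse causation would undermine both uses.

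**Working it through.** **1. Expected events.** Inputs from section 4.1.1: 67% high risk at 2.8%, 33% low risk at 0.6%.
- Two-proportion formula, pooled variance, no continuity correction, two-sided 5%, 80% power: 882 high-risk patients, 882 × (1 + 33/67) ≈ 1316 in total. Power at 1308 is 79.7%. The stated 1308 is reproduced to within 1%.
- Overall risk: 0.67 × 0.028 + 0.33 × 0.006 = 0.02074.
- Events: 1308 × 0.02074 = 27.1; 1350 × 0.02074 = 28.0.
- The Hanley-McNeil interval for an AUC of 0.75 with 27 events is 0.64 to 0.86, as stated.

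With 27 or 28 events, a handful of contaminated cases matters.

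**2. Order of exposure and outcome.** Countable events start at 48 h from admission. Wear starts at inclusion, up to 72 h from admission, and runs to discharge or transfer. For any event inside that span, wear after the event belongs to the recording, and no stated rule removes it. If inclusion is late, an event at 48 to 72 h can precede all wear.

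**3. Size when mobility has no true effect.** Simulation of 1308 patients with 27 events. True activity X is log-normal (log-SD 0.7) and unrelated to VTE. For events during wear, observed activity = X × (1 − f × d), where f is the share of wear after the event and d the relative fall in activity. The documents give none of these inputs; assumed ranges are mean f 30 to 70% and d 50 to 80%. The test is a rank test with null standard error of the AUC √[(N+1)/(12·e·(N−e))] = √[1309/(12 × 27 × 1281)] = 0.056.

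| Events during wear | Mean AUC | Risk ratio, lowest vs highest quartile | Significant at 5% |
|---|---|---|---|
| 10% | 0.505–0.531 | 1.04–1.28 | 5–8% |
| 25% | 0.514–0.576 | 1.14–1.82 | 6–27% |
| 50% | 0.534–0.644 | 1.35–3.04 | 10–73% |
| 75% | 0.552–0.725 | 1.58–6.19 | 14–98% |
| Pre-event wear only | 0.50 | 1.00 | 4.8% |

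A rerun of the 10%, 25% and 50% rows and the null agreed to within about 0.01 in AUC and 4 percentage points in the rejection rate. If activity instead rises by 50% after the event (50% of events during wear, half the wear after the event), the mean AUC is 0.455: the bias reverses.

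**4. Events lost to a landmark.** Loss = in-hospital events × (mean ward time from 48 h to landmark ÷ mean ward time after 48 h). Assumptions: 27 events, 30 to 50% in hospital, log-normal stay with median 6.5 days and log-SD 0.5 to 0.7, constant hazard after 48 h.

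| Enrolment after admission | 24 h window | 48 h window |
|---|---|---|
| 24 h | 0 | 1.2–2.4 |
| 48 h | 1.2–2.4 | 2.2–4.7 |
| 72 h | 2.2–4.6 | 3.1–6.6 |

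Example (72 h, 24 h window, log-SD 0.5, 50% in hospital): 13.5 × 0.34 ≈ 4.6.

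**The case against.** The protocol never says that mobility is averaged over the whole stay, and which wear days feed the predictor could be set in an analysis plan that is not shown. That is fair: the whole-stay level is the natural reading, but it is inferred. What stands is that the wear rule and the models as written do not deliver the ordering that section 6.1 claims, and the two compared measures are timed differently on the face of the protocol.

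Contamination is also limited. Wear stops at transfer, for example to intensive care, and a patient who dies at the event has no later wear. A patient with a VTE diagnosed before enrolment would often meet the exclusion for therapeutic anticoagulation, so a recording that lies wholly after the event should be uncommon. These points reduce the bias but do not remove it.

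A reader might infer more than the documents support:
- That objective immobility will look predictive. Size and direction depend on the share of events during wear and on how activity changes afterwards; neither is given.
- That prophylaxis is defined as use at any time in the stay. The words "start date and type of TPX, defined as any use of pharmacological" in section 3.3.3.1 introduce a list of modalities within baseline collection and say nothing on timing.
- That longer recording by itself favours accelerometry. Daily measures are rates; more days mainly reduce noise, and no separate bias has been shown.

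**Conclusion.** The point holds as a risk of bias in both work package 2 objectives. Under no true association, the mean AUC moves from 0.50 to about 0.51–0.58 if a quarter of events occur during wear, and to about 0.53–0.64 if half do. Against a null standard error of 0.056, that runs from a negligible shift to a frequent false positive. The figures illustrate assumed inputs; the absence of a cut at the event and the mismatch in timing do not depend on them. Work package 1, and with it the primary objective, is untouched. This should be corrected before analysis, but it does not threaten the study as a whole.

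**What to change.** In sections 3.3.3.2 and 4.1.2:
- Define the primary objective mobility measure from a fixed early window, for example the first 24 h of valid wear, which is already the minimum.
- Start follow-up for the objective and the subjective measure at the end of that window, and use only physician ratings made by then.
- Exclude from this analysis patients with VTE or death before that time, and use no wear time after a VTE diagnosis.
- Keep longer-duration mobility as a time-updated covariate built from pre-event data, in a cause-specific model.
- Bring the wording of section 6.1 into line.

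Cutting wear at the event is not enough alone. Cases would then be averaged over earlier and shorter periods than non-cases, and any trend in activity over the stay would appear as an association.

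The cost is analysis wording; raw accelerometer files and event dates are already collected. Two losses should be stated. Events before the landmark leave work package 2: up to about 5 of 27 with a 24 h window and up to about 7 with a 48 h window under the assumptions above, worst when enrolment is late. A short window also does not capture the 3-day and 7-day duration criteria of the risk scores, so the early measure is a different construct from the item that it replaces.

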### ***Risk stratification to predict HA-VTE using innovative strategies***

Recently, objective measures of mobility using accelerometry, which allows the collection of objective and continuous physical activity data, improved the accuracy of mobility assessment in hospitalized patients. Observational studies showed that medical inpatients are immobile most of the time, defined as being confined to a bed or chair. In a sample of hospitalized older patients capable of walking independently prior to admission, the mean time per day spent standing or walking was 43 min. Another study reported similar durations spent walking (7 min./day) and standing up (35 min./day) in 100 older patients. A recent study performed in a Swiss hospital by one of the PIs confirmed that hospitalized medical patients aged  $\geq 65$  years moved very little during a hospital stay. Interestingly, patient's mobility peaked during mealtimes, indicating that patients were actually able to move (**Figure 2**).

While a meta-analysis of epidemiological studies identified a 2- to 3-fold increase in VTE risk in immobilized medical patients, these findings were limited by the heterogeneity in methods and inaccuracy of mobility assessment. One study with objective accelerometry-based mobility measurements in 102 patients considered HA- VTE as a secondary outcome, but the sample size was too small to draw any meaningful conclusions. An objective evaluation of mobility and dose-dependent threshold to identify patients at high VTE risk has never been explored in the field of VTE prevention, neither compared to the current risk stratification strategies for HA-VTE. Whether novel, objective mobility measures such as accelerometry could predict HA-VTE, and whether incorporation of these objective measures into existing RAMs could improve their predictive ability, must therefore be examined.

**Figure 2. Average mobility per hour among patients hospitalized in an internal medicine unit at the Lausanne University Hospital (CHUV).**

[figure not shown]

Results are shown as average and with 95% confidence interval. Average vector magnitude is an estimate reflecting total ambulatory movement over the observation period, i.e. it is a proxy for mean activity levels.

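### Work package 2: free choice of wrist, with no rule for arm paresis and no check of steps against recorded walking ability, allows mobility error that differs between patients

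*Protocol*

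**What the plan says.** Section 3.3.3.2 measures mobility "using a wrist-worn tri-axis accelerometer". On placement it says that "patients will choose on which wrist they prefer to wear the device", and then: "Previous studies have shown that measuring site does not influence measurement". The reference for that statement is, by its title, a comparison of the dominant with the non-dominant wrist.

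Steps are extracted by software, and the share of mobile time is estimated "using a cut-off of <4 steps and ≥4 steps taken per minute to define periods of immobilization and mobilization respectively". A study of medical inpatients is cited as precedent for the cut-off. The same section lists other measures from the same device: active and inactive minutes, mean acceleration, steps per day, cadence and gait speed.

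The section also records at baseline whether each patient walks independently, with help, with or without aids, or not at all. Table 4 (section 3.3.3.1) records stroke and hemiplegia. Neither is linked to the placement of the device or to the step data.

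Section 4.1.2 analyses mobility as a continuous measure and in quartiles, adjusted for thromboprophylaxis and site. It seeks an immobility cut-off by time-dependent ROC analysis, then compares the objective with the subjective measure by likelihood ratio tests or AIC, c-statistics and the net reclassification index.

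**The concern.** Work package 2 asks whether accelerometry predicts hospital-acquired VTE better than the physician's perception of mobility. The answer depends on how patients are ordered by the device.

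A patient with hemiplegia or arm weakness after stroke may wear the device on the affected side and appear less mobile than he or she is. A patient whose hands rest on a walking aid may lose steps in the same way. That mechanism is technical reasoning, not something the protocol states. Both kinds of error would fall on identifiable groups. Lower-limb paresis, recent stroke and immobilization are themselves items in the scores of Table 1, so the error may be related to VTE risk, and the direction of the bias cannot be foreseen.

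The cited wrist comparison does not, by its title, cover a paretic arm. The other wrist-derived measures share the placement problem, so turning to mean acceleration or active minutes does not remove it.

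The expected amount of walking is small, so even low error rates matter. If the error is not measured, a result for or against accelerometry could not be separated from sensor error.

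**Working it through.** The protocol gives no figure for the accuracy of step detection, so there is none to reproduce. Work package 2 takes over the sample size of work package 1, which is not in dispute. At the section 4.1.1 rates, the expected number of events is 1308 × (0.67 × 0.028 + 0.33 × 0.006) = 27.1.

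**Inputs from the protocol**
- Walking time, section 1.1: "Another study reported similar durations spent walking (7 min./day) and standing up (35 min./day) in 100 older patients".
- A wider definition of mobile time, same section: "the mean time per day spent standing or walking was 43 min".
- Wear time, section 3.3.3.2: "Patients will be asked to wear the device continuously (day and night, including showering) until hospital discharge", so up to T = 1440 min/day. The minimum for a valid day is 10 h of daytime wear, so T = 600.

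**Assumption, not in the protocol:** the share f of non-mobile minutes that reach 4 apparent steps, taken from 0.1% to 2%.

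**Formulas**, with w true mobile minutes, all detected:
- False mobile minutes = f × (T − w)
- False share = false / (false + w)

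Each cell shows false minutes per day and the false share.

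| f | w = 7, T = 1440 | w = 7, T = 600 | w = 43, T = 1440 |
|---|---|---|---|
| 0.1% | 1.4 (17%) | 0.6 (8%) | 1.4 (3%) |
| 0.5% | 7.2 (51%) | 3.0 (30%) | 7.0 (14%) |
| 1% | 14.3 (67%) | 5.9 (46%) | 14.0 (25%) |
| 2% | 28.7 (80%) | 11.9 (63%) | 27.9 (39%) |

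False minutes become the majority when f exceeds w / (T − w): 7/1433 = 0.49%, 7/593 = 1.18% and 43/1397 = 3.08% respectively.

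**Common against differing error.** Take patient A walking 7 min/day and patient B walking 14 min/day, both worn for 24 h with f = 0.5%.
- Same error for both: A records 7 + 0.005 × 1433 = 14.2 min; B records 14 + 0.005 × 1426 = 21.1 min. Both are inflated, but the order is kept, and a cut-off chosen from the data moves with them.
- Half of B's walking is missed (assumed): B records 7 + 7.1 = 14.1 min. A twofold true difference disappears.
- None of B's walking registers (the extreme for a paretic arm): B records at most the 7.1 false minutes and ranks below A.

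No choice of cut-off on the recorded scale restores the order in the last two cases.

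**The case against.** The strongest reply is that the 4-step rule is only one output among several. Section 4.1.2 uses mobility as a continuous measure and in quartiles and finds its own cut-off, and a precedent in inpatients is cited. This stands as far as it goes: an offset shared by all patients would do little harm to prediction. It does not answer error that differs between patients.

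The size also rests on assumed rates. The 7 min/day comes from 100 older patients, whereas this study enrols adults from 18. With 43 min/day, or only 10 h of wear, the false share is much lower. That stands too.

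Three stronger readings are tempting, and the protocol does not support them.
- A reader might infer that mobile minutes will be mostly false. No false-step rate is given, so this cannot be concluded.
- A reader might take the statement on measuring site as a claim that a wrist can replace a leg. It directly follows the sentence on choice of wrist, and the cited dominant versus non-dominant comparison fits that meaning.
- A reader might take the observation in section 1.1 that "patient's mobility peaked during mealtimes, indicating that patients were actually able to move" as proof that eating produces false steps. The figure behind it shows vector magnitude, not steps, and getting up for meals explains it equally well.

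Finally, subgroup reporting may belong in a statistical analysis plan that is not shown. The choice of wrist, however, is fixed in the protocol itself. How many patients have arm paresis is not stated, and they need not choose that arm.

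**Conclusion.** The point holds in a limited form. The protocol leaves device placement to patient preference, without a rule for arm paresis, and does not use recorded walking ability to check the steps. The resulting error can differ between patients, and the ROC cut-off cannot correct it.

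Its size is unknown. Over the assumed 0.1% to 1% per-minute rates, the false share of mobile minutes runs from about 17% to 67% at 7 min/day and from about 3% to 25% at 43 min/day, both with 24 h wear. These figures show how sensitive the measure is, not how wrong it will be. Only work package 2 is affected. The change is worth making because it costs very little and the error cannot be judged without it.

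**What to change.** 1. In section 3.3.3.2, replace free choice with: *device on the non-paretic wrist where there is arm paresis, otherwise the patient's choice; side recorded.* If the next sentence is touched, change measuring site to choice of wrist.
2. Before any link to VTE data, report the minutes with at least 4 steps in patients recorded as not able to walk, as a check on false steps. State its limits: these patients may move their arms less than walkers do, and walking ability may change during the stay.
3. Report the work package 2 results by walking-aid use as a sensitivity analysis. Keep the 4-step cut-off, so that results stay comparable with the cited study.

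The cost is one line in the device instructions, one recorded item and a little analysis of data already collected. With about 27 events expected in total, the results by walking-aid use will be imprecise and should be read as descriptive.
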